### Inclusion Criteria

Inclusion criteria include adults ≥ 60 years old with confirmed diagnosis of cirrhosis (Child Pugh Class A, B, or C) and a liver frailty index (LFI) ≥ 3.8. Participants must also be up to date on variceal screening through either up-to-date endoscopy screening and/or surveillance or on beta blocker. All participants require access to a digital device and internet, ability to remain in the study for at least 3 months, and engagement in ≥ 80% of activities in the ramp-up period before enrollment into STRIVE.

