### Measurements

#### Assessments

Baseline assessment will be completed prior to pre-enrollment into the ramp-up period (Fig. 3). Additional follow-up assessments will be completed at 6 weeks after enrollment into the study and 12 weeks at completion of the study. Assessment at baseline will include demographic characteristics, vital signs and physical exam, and the following questionnaires: Patient Reported Outcomes Measurement Information System (PROMIS-29 v 2.0) to measure health-related quality of life^30^ (HrQoL), Godin-Shephard Leisure Time Physical Activity Index (LTPA)^31^ and Duke Activity Status Index (DASI)^32^ to measure self-reported physical activity, the Patient Activation Measure (PAM^®^)^33^ to measure patient activation, and DietID^™^
^34^ and the Automated Self-Administered Dietary Assessment Tool (ASA24)^35^ to measure dietary patterns. PROMIS-29 v2.0 is an NIH-supported HrQoL measure of 29 questions that cover broad domains including physical function, anxiety, depression, fatigue, sleep disturbance, participation in social roles and activities, and pain intensity with built-in normative references to the US general population.^30^ The LTPA is a 3-question survey that measures how much strenuous, moderate, and mild exercise a person completes in a 7-day period. A weekly leisure-time activity score is calculated to categorize a patient’s activity level.^31^ The DASI is a validated 12-question survey designed to estimate a patient’s functional capacity.^32^ The Patient Activation Measure is a 13-item survey to measure a patient’s knowledge, skill and confidence in managing one’s own health and healthcare. Patients are categorized into 4 levels: Disengaged and overwhelmed, becoming aware but still struggling, taking action and gaining control, and maintaining behaviors and pushing further.^33^ DietID^™^ uses the patented Diet Quality Photo Navigation (DPQN^®^), which uses pattern recognition instead of dietary recall or food logs to provide a dietary assessment.^34^ Patients are presented composite images of established dietary patterns and are asked to select images most like their own, current food intake until a best fit is achieved. Outputs include the Healthy Eating Index (HEI-2020) and nutrient analysis. The ASA24 is a self-administered 24-hr recall dietary assessment developed by the National Cancer Institute.^35^

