### Sample size

We aim to randomize 200 total participants (100 per arm) for this study. Calculations were performed using PASS sample size software and were based on two-sample t-test assuming equal variances with a significance-level of α = 0.05, testing the difference between two means, e.g., change in LFI between start of study and study completion between participants randomized to creatine/whey protein supplementation vs. placebo. Based on published cohorts that report a mean LFI of 3.8 (SD 0.72–0.77) in similar populations,^40^ the common standard deviation for both groups is assumed to be 0.75. The proposed sample size is powered at 80% to detect a mean change in LFI in the creatine/whey supplementation group that is 0.3 LFI-units greater than the mean change in LFI in the placebo group. We have previously found that a change in LFI of 0.3 units is associated with improved survival.^39^

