### Statistical analysis

Analyses will be evaluated in the intention-to-treat population (all randomized participants). For the primary analysis, change in frailty (LFI) between the beginning of the study and study completion will be calculated for all participants, and the mean change will be modeled using a linear regression model that includes terms for trial arm (creatine/whey protein supplementation vs. placebo) and variables used in the randomization procedure (Child Pugh score and gender).^41, 42^Continuous secondary outcomes will be analyzed in the same way. In addition, changes in frail status (LFI ≥ 4.4) between the beginning of the study and study completion will be modeled using a logistic mixed effects regression model that includes fixed effects for trial arm and variables used in the randomization procedure and random effects for each participant to account for the within-participant correlation.

Exploratory models may adjust for prognostic variables and/or baseline variables that exhibit imbalance due to chance[cite]. Additional as-treated or per protocol analyses may be performed.

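### The additional frail-status model lists no visit or arm-by-visit term, so with baseline and completion rows its arm coefficient is not the effect on change and is diluted to roughly 40–50% of the week-12 log-odds ratio

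*Protocol article*

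**What the plan says.** The Statistical analysis section of the Protocol article sets the target as "changes in frail status (LFI ≥ 4.4) between the beginning of the study and study completion". The tool is a "logistic mixed effects regression model that includes fixed effects for trial arm and variables used in the randomization procedure"; the randomisation variables are Child Pugh class and gender. The model also has "random effects for each participant to account for the within-participant correlation". Neither visit nor an arm-by-visit interaction is listed.

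On timing, the Assessments section states: "Baseline assessment will be completed prior to pre-enrollment into the ramp-up period". Randomisation follows the ramp-up, so baseline frail status precedes allocation. The same section adds: "Additional follow-up assessments will be completed at 6 weeks after enrollment into the study and 12 weeks at completion of the study".

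The primary analysis, in the same paragraph, is built differently. It computes one LFI change score per participant and regresses it linearly on arm and the two stratification factors.

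**The concern.** In the primary model the outcome is already a change, so the arm coefficient is the treatment effect on change. The frail-status model uses the same list of fixed effects, but its outcome appears to be frail status at each visit. With repeated rows, arm alone no longer represents an effect on change.

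What is at stake is the frail-status result itself. The reported odds ratio would blend a comparison made before treatment with one made after it, would be pulled towards 1, and would have less power than a correctly specified model on the same data.

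**Working it through.** **1. The plan's own figure.** The Sample size section uses a "two-sample t-test assuming equal variances with a significance-level of α = 0.05", a difference of 0.3, and states that "the common standard deviation for both groups is assumed to be 0.75". Two-sided testing is assumed.

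- n per arm = 2 × (1.960 + 0.842)² × 0.75² / 0.3² = 98.1, rounded up to 99 (198 in total, against 200 planned).
- Power at 100 per arm: 0.3 / (0.75 × √(2/100)) = 2.83; Φ(2.83 − 1.96) = 80.7% (80.4% by exact t).

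The figure reproduces. It applies to mean LFI change only; the plan gives no power figure for frail status.

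**2. Which data layouts fit the stated model?**

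- *Baseline and completion rows.* This fits the named time points and the stated reason for the random effect. One arm coefficient then covers both visits.
- *One change indicator per participant.* There is no within-participant correlation left to model, and a random intercept is not identifiable.
- *Week-6 and week-12 rows only.* Initial status is absent, so change is not modelled, and the named time points are not the ones used.

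No layout makes the listed terms estimate a change by arm. The first is the natural reading and is carried forward.

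**3. First-order size.** If the arm log-odds ratio is 0 at baseline and δ at week 12, a single arm coefficient is near (0 + δ)/2 = 0.5δ. Omitting the visit effect tends to shrink it further.

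**4. Large-sample fits.** Inputs from the plan: LFI floor at entry ("a liver frailty index (LFI) ≥ 3.8"), cut-point 4.4, SD 0.75, difference 0.3. Assumed: baseline LFI normal(3.8, 0.75) truncated at 3.8, SD of change 0.75, and the placebo change shown. Stratification factors are left out because they are balanced by design. Each model is a random-intercept logistic model fitted by maximum likelihood with Gauss–Hermite quadrature.

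| Placebo change | Arm-only log-OR (OR) | Arm-by-visit log-OR (OR) | Ratio |
|---|---|---|---|
| 0 | -0.42 (0.66) | -0.85 (0.43) | 0.49 |
| -0.3 | -0.37 (0.69) | -0.86 (0.42) | 0.43 |

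Varying the SD of change from 0.35 to 0.75 and the placebo change from 0 to -0.3 gives ratios of 0.24 to 0.49. The lowest comes from the smallest SD with the largest placebo change. Generating data directly from a logistic random-intercept model gives 0.257 to 0.499.

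**5. If week-6 rows are also used.** The LFI-based ratio is 0.29–0.52 with half the effect present at week 6, and 0.30–0.69 with the full effect present. First-order values are (0 + 0.5 + 1)/3 = 0.50 and (0 + 1 + 1)/3 = 0.67.

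**6. Power at 100 per arm**, from Φ(|coefficient|/SE − 1.96). Example with a week-12 log-OR of -0.85, random-intercept SD 1.8 and no placebo visit effect:

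- arm only: 0.399/0.358 = 1.11, power 20%;
- visit and arm-by-visit added: 0.85/0.521 = 1.63, power 37%;
- the same with a common baseline: 0.85/0.435 = 1.95, power 50%.

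Over four such scenarios the ranges are 19–24%, 36–59% and 48–70%. A separate simulation (200 trials per scenario, baseline to week-12 correlation 0.5 and 0.7) gave ratios of 0.372/0.869 = 0.43 and 0.493/1.150 = 0.43. Its power was 22% and 29% for arm only, 40% and 56% for plain arm-by-visit, 60% and 73% with a common baseline, and 61% and 75% for week-12 logistic regression adjusted for baseline LFI.

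**The case against.** The strongest reply is that a journal article condenses. The sentence says what the model includes, not that nothing else enters, and a model of change between two named times may be taken to imply a visit effect. Row structure and the tested contrast often sit in a SAP, which is not shown. This would carry weight if the article had named only the model class. It does not carry here: the sentence gives the outcome, both time points, the fixed effects, the random effects and the reason for them, and anyone who fits what is listed gets the wrong coefficient.

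Other parts of the reply do stand:

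- The analysis is an addition. Frail status is not among the secondary outcomes in the Study Outcomes section, and the sample size does not rest on it.
- A reader might infer that the trial would miss a real benefit. The document does not support that, because the powered primary analysis of LFI change is correctly formed for its purpose and would still report the benefit.
- A reader might blame the missing terms for the whole gap between 22–29% and 60–75% power. Part of that gap is the efficiency gained from using baseline; the plain arm-by-visit term reaches only about 40–56% in the same simulation.
- A reader might conclude that the effect is always more than halved. At the plan's SD with no placebo change the ratio is 0.49, essentially one half, and it can reach about 0.69 if week-6 rows enter with the full effect present.
- The error attenuates towards the null, so it does not create a false benefit.

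**Conclusion.** The frail-status model is wrong as written. With rows at the two named time points, its arm coefficient pools a contrast that is zero in expectation with the week-12 contrast and does not estimate the effect on change in frail status. It retains roughly 40–50% of the week-12 log-odds ratio under plausible assumptions, and less when change in LFI is less variable and frailty also falls on placebo. Dilution and lower power appeared in every two-visit scenario examined. The exact size rests on quantities the document does not give: the placebo change, the within-person variability, the share of participants who are frail, and whether week-6 rows are used. Because the analysis is neither primary nor a listed secondary outcome, this is a should-fix point. It gives no ground for doubting the primary LFI analysis or the sample size.

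**What to change.** Change one sentence in the Statistical analysis section, before unblinding, in one of two ways:

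- Keep the mixed logistic model, add fixed effects for visit and arm-by-visit (optionally with a common baseline mean across arms), state which visits supply rows, and name the week-12 arm contrast as the treatment effect.
- Replace it with logistic regression of week-12 frail status on arm, baseline LFI, Child Pugh class and gender, with no participant random effect.

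Either is acceptable. Their odds ratios condition on different things (the participant's random effect, or baseline LFI), so the plan should commit to one. The cost is the wording only: no extra visits, data or participants, and the primary analysis stays as it is.

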## Methods/Design

### Study design and setting

We will conduct a prospective double-blind placebo-controlled, two-arm randomized controlled trial at a single center (Fig. 1). To ensure patients in the study are able to navigate the STRIVE platform and perform exercises on STRIVE, all eligible patients will first be pre-enrolled in a two-week “ramp-up” period during which they will participate in a simplified version of the digital health program that includes weekly exercise videos, post-video surveys, and weekly telehealth check-ins with a physician and/or exercise specialist to monitor their weekly exercise and adjust exercise prescriptions as needed. Patients who achieve ≥ 80% engagement with app activities and scheduled check-ins during the ramp-up period will proceed to randomization. Patients enrolled in the study will be randomized to creatine/whey protein supplementation vs placebo supplementation and STRIVE digital health programming. The STRIVE digital health programming uses the same interface as the ramp-up but includes three pillars: exercise, nutrition, and life skills (Fig. 2). Activities in the app include pre-recorded exercise videos to be completed three times per week, educational videos and reading, and interactive quizzes and surveys. Patients also receive weekly physician or exercise specialist check-ins to monitor exercise progression and to recommend personalized modifications; weekly check-ins with clinical research coordinator for safety monitoring, app-related questions, and supplement adherence evaluation; and biweekly check-ins with a nutritionist to assess dietary habits and provide personalized dietary recommendations. Patients are evaluated in-person at baseline prior to the ramp-up period, at 6 weeks after enrollment into STRIVE, and at 12 weeks at completion of STRIVE.

LFI: liver frailty index, PAR-Q: Physical Activity Readiness Questionnaire for Everyone, PROMIS-29 v2.0: Patient Reported Outcomes Measurement Information System, DASI: Duke Activity Status Index, BIA: Bioimpedance analysis

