### Creatine/whey protein and placebo supplementation

Creatinine/whey protein and non-sugar based placebo powder supplementation will be provided at a dosage of 5g creatine and 35g whey protein daily or one daily serving of placebo powder respectively given 30 minutes prior to exercise on exercise days and anytime on days without exercise.^36^ This dose was determined based on general doses of creatine and/or whey protein supplementation provided in other studies among athletes and older adults.^27, 37^ Kidney and liver function will be evaluated at baseline, 6 weeks, and 12 weeks. Participants who develop a ≥ 5 times increase from baseline or upper limit of normal of AST/ALT, ≥ 1.5 times increase of creatinine, or any grade 3–4 laboratory abnormality will be evaluated for dose reduction or discontinuation. If patients experience moderate gastrointestinal symptoms interfering with daily activities, persistent muscle cramps, or ≥ 5 pound weight gain over 1 week with concern for fluid retention, participants will initially undergo reduction of supplementation to half dose at week 1 week and re-escalation to full dose at week 2 if symptoms resolve. If symptoms persist at half dose, supplementation is discontinued and patients will continue STRIVE digital health programming.

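### The optional as-treated analysis would regroup participants by a health-dependent stopping rule and, if those who stop fare worse, show a false benefit; intention-to-treat is unaffected

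*Protocol article*

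**What the plan says.** The Statistical analysis section sets intention-to-treat, in all randomised participants, as the analysis population. Its closing sentence is "Additional as-treated or per protocol analyses may be performed". The article defines neither of the two.

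The section on creatine/whey protein and placebo supplementation describes how a participant may come off product. Rises in AST/ALT or creatinine, or any grade 3–4 laboratory abnormality, lead to evaluation for reduction or discontinuation. Gastrointestinal symptoms, persistent cramps, or rapid weight gain with concern for fluid retention lead first to half dose. Then: "If symptoms persist at half dose, supplementation is discontinued and patients will continue STRIVE digital health programming". The rule is not limited to one arm, and the trial is double-blind.

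The Study design and setting section provides "weekly check-ins with clinical research coordinator for safety monitoring, app-related questions, and supplement adherence evaluation", so adherence is already assessed weekly.

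**The concern.** An as-treated comparison groups people by the product they took instead of the arm they were assigned. Here, product taken depends on health after randomisation. Some triggers, notably creatinine, grade 3–4 laboratory values and fluid gain, are plausible markers of worsening liver disease in a population that includes Child Pugh B and C. The Background section itself links decompensation to worse frailty.

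The regrouping goes one way. An active participant who stops can move into the untreated group. A placebo participant who stops is already there, and the article gives placebo participants no route to active product. If stoppers do worse on LFI whatever powder they took, the active group loses its worst-faring members and the untreated group gains them.

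At stake is a secondary estimate of the effect in people who took the product. That is the figure a reader would look to if the intention-to-treat result were null or diluted.

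**Working it through.** **The plan's own figure.** Inputs from the Sample size section: "two-sample t-test assuming equal variances with a significance-level of α = 0.05" (taken as two-sided), SD 0.75 ("the common standard deviation for both groups is assumed to be 0.75"), a difference of "0.3 LFI-units greater than the mean change in LFI in the placebo group", and 100 per arm. The normal approximation gives 99 per arm for 80% power. The t-test gives 79.97% at 99 per arm and 80.4% at 100, so the stated size reproduces. These figures set the scale for what follows.

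**Assumptions not in the article.** The product has no effect. A fraction d stops in each arm. Stoppers' LFI change is worse by D (higher LFI is worse). Everyone is followed for LFI. Active stoppers are counted as untreated.

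**As-treated bias under no effect**, with n per arm and continuers' mean change set to 0:

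- Treated group: n(1−d) active continuers, mean 0.
- Untreated group: n placebo participants with mean dD, plus nd active stoppers with mean D. The sum is ndD + ndD = 2ndD over n(1+d) people.
- False benefit = 2dD/(1+d).

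| d | D | 2dD/(1+d) | Share of 0.3 target | Two-sided rejection, simulated |
|---|---|---|---|---|
| 5% | 0.3 | 0.030/1.05 = 0.029 | 10% | 6% |
| 10% | 0.2 | 0.040/1.10 = 0.036 | 12% | 6% |
| 20% | 0.4 | 0.160/1.20 = 0.133 | 44% | 23% |
| 30% | 0.6 | 0.360/1.30 = 0.277 | 92% | 67% |
| any | 0 | 0 | 0% | 5% |
| 20% | −0.3 | −0.120/1.20 = −0.10 (against active) | – | 14% |

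The simulations used 100 per arm, SD 0.75 and a pooled t-test, with 4,000 or 5,000 trials per setting. Mean as-treated estimates agreed with the formula. Intention-to-treat stayed centred on 0 with about 5% rejection throughout.

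**Per-protocol, same assumptions.** Stoppers are removed from both arms, so both means are 0 and there is no bias. The simulations confirm this. Bias would need stopping rates, or the kind of person who stops, to differ by arm.

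**With a true effect of 0.3 in takers and none in stoppers** (d = 20%, D = 0.4):

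- As-treated: 0.3 + 0.133 = 0.433 (simulated 0.434).
- Intention-to-treat: 0.8 × 0.3 = 0.24.
- Complier-average: 0.24/0.8 = 0.30 (simulated 0.298).

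**What the complier-average estimate costs.** The standard error of the intention-to-treat difference is 0.75 × √(2/100) = 0.106, a 95% half-width of about 0.21. Dividing by 0.8 gives about 0.26. If stoppers gain half the benefit from product taken before stopping, intention-to-treat is 0.8 × 0.3 + 0.2 × 0.15 = 0.27. The estimate is then 0.27/0.8 = 0.34, not 0.30.

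**The case against.** The strongest reply is that nothing important depends on this sentence. The analysis is optional and undefined, and it sits behind an intention-to-treat primary analysis. Its definition may be in an analysis plan that is not shown. If as-treated kept stoppers in the group of the product they first received, this mechanism would not arise. That stands as a limit on severity. It does not remove the point: placebo participants have no stated route to active product, so, rare dispensing errors aside, an as-treated analysis departs from intention-to-treat only by regrouping on product taken.

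A reader might infer that product is stopped for decompensation and that the bias is therefore known to favour the supplement. The article does not support this. The supplementation section does not mention decompensation. Laboratory triggers lead to evaluation, and symptom triggers to half dose before any stop. Gastrointestinal symptoms and cramps are mainly tolerability signs. The Exclusion Criteria also treat renal effects and edema as possible effects of the supplement itself. The direction therefore holds only if stoppers fare worse, and the article gives neither how many stop nor how they fare.

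A reader might also extend the charge to per-protocol. With equal stopping in both arms it does not apply. If the supplement itself causes fluid gain or creatinine rise, stopping could differ by arm, but the calculations here do not cover that case.

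**Conclusion.** The point holds in conditional form and is minor. If active stoppers are regrouped as untreated and fare worse, the as-treated option produces a benefit from an inert product. Under the assumed values this runs from about 0.03 LFI units, which is negligible, to about 0.28, close to the whole target effect. It vanishes if stoppers fare the same and reverses if they fare better. The size rests on d and D, which are assumptions, and on equal stopping in the two arms. The article does not show that a false benefit will occur, and the primary intention-to-treat conclusion is unaffected. The reason to act is that the article names a method that breaks randomisation where treatment received depends partly on health, and an alternative that keeps randomisation is available from data already collected.

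**What to change.** Drop the as-treated option. If an on-product effect is wanted, replace the sentence with wording such as: *The effect in participants who take the product will be estimated as a complier-average effect, with randomised arm as instrument, the covariates of the primary model, and a binary adherence definition fixed before unblinding. Any per-protocol analysis will be labelled exploratory.*

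If graded exposure is preferred, for example to count product taken before a reduction or stop, call the result an instrumental-variable dose estimate and state its linear dose-response assumption. It is then no longer a complier average.

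The cost is a sentence or two of text and an agreed adherence threshold applied to the weekly record. The price in inference is a wider interval and the exclusion restriction, that assignment acts only through adherence as defined. The blinded placebo supports that restriction, but it fails to the extent that participants classed as non-adherent still benefit from partial product. No change to dosing or stopping rules is implied.
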